#### Open exposure-based therapy

Transdiagnostic EBT will be delivered by experienced, license-eligible clinicians. To aid generalization to EBT delivered in clinical practice, the study clinician will develop a personalized assessment and treatment plan for each participant. Assessment algorithms will (1) guide the case formulation, which emphasizes threat appraisals as maintaining factors to be targeted during treatment; and (2) provide the data for tracking success and progress. The case formulation guides the clinician in the development of personalized exposure exercises, while tracking success and progress allows for updating of the case formulation and fine-tuning of the treatment plan. Consistent with contemporary models of EBT [31, 110], exposure practice aims to help patients relearn a sense of safety around feared cues. Hence, exposure exercises are planned to ensure violation of threat expectancies. In addition to ensuring sufficient activation of the “fear network” and a focus on repetition to provide disconfirmatory evidence, exposure practice will be planned and delivered keeping in mind that fear extinction tends to be context specific. Specifically, practice will occur across relevant contexts both within and outside the session (i.e., homework) and clinicians will guide participants in processing their exposure practice to facilitate consolidation of safety learning.

To achieve these ends, study clinicians will use a manual that describes these procedures for treatment planning and delivery. The manual “Personalized Exposure Therapy: A Person-Centered Transdiagnostic Approach [32]” includes clear guidance on the conceptual model of EBT, assessment planning and strategies, and separate chapters on the planning and delivery of in vivo, imaginal and interoceptive exposure practice, respectively. The treatment dose will be set at 12 one-hour sessions, delivered over the course of 12 weeks. The quality assurance protocol for treatment implementation involves requiring all clinicians to (1) complete a 6-h training workshop; and (2) attend weekly supervision meetings.

### Assessment

Table 1 provides an overview of assessment targets and measures by study phase.

#### Screening

The online questionnaire first asks potential participants to provide standard demographic information and to indicate whether they have experienced or been diagnosed with any of the psychiatric or medical exclusion criteria. Participants who do not endorse exclusion criteria will then be asked to complete the OASIS [107]. Participants who endorse experiencing anxiety-related symptoms and impairment will then complete the DSM-5-TR Self-Rated Level 1 Cross-Cutting Symptom Measure [111]. Based on their responses to this measure, participants will also complete relevant Level 2 or diagnosis-specific measures, which for the current study include the Severity Measure for Panic Disorder [112], Mobility Inventory (MI; alone) [113], Social Phobia Inventory (SPIN) [114], PROMIS Emotional Distress—Anxiety—Short Form [115], Dimensional Obsessive Compulsive Scale [DOCS; OCD] [116], and the PTSD Checklist for Diagnostic and Statistical Manual of Mental Disorders-Fifth Edition (PCL-5) [117] as well as measures of constructs that aid the case formulation (e.g., anxiety/fear cues, core threat appraisals, and safety behaviors). Participants that do not meet any exclusion criteria after this screening will be given the option to schedule an in-person screening visit.

The clinician assigned to the participant will complete the in-person screen visit, which includes administration of the Structured Clinical Interview for DSM-5 (SCID-5) [118] and the Columbia Suicide Severity Rating Scale (C-SSRS) [108].

#### Biomarker measures

For each VC inhalation, mean and peak reactivity will be assessed across different epochs (i.e., baseline, anticipation, peak response, and recovery). For the subjective anxiety index, difference scores will be calculated between the 1^st^ trial (bag of compressed air) and 2^nd^ trial (bag of CO_2_). The primary subjective measure of CO_2_ peak anxiety reactivity will be the participant’s peak real-time ratings of subjective anxiety (reported throughout the trials using the rating dial). The primary measure of the degree of habituation vs. sensitization will be the change in peak subjective anxiety from the 1^st^ to the 3^rd^ of the CO_2_ provocations. The primary behavioral measure will be avoidance responses (latency in seconds between inhalations 1–2, and 2–3). The primary physiological measure will be the difference in end-tidal CO_2_ during the resting baseline vs. recovery phase.

For each of the three VH provocations, mean and peak reactivity will also be assessed across epochs (i.e., baseline, anticipation, peak response, and recovery). For the subjective index, difference scores will be calculated between VH baseline (at rest) ratings and the trial (VH) ratings. The primary subjective measure of VH peak anxiety reactivity will be the participant’s peak real-time ratings of subjective anxiety (reported throughout the trials using the rating dial). The primary measure of the degree of habituation vs. sensitization will be the change in peak subjective anxiety from the 1^st^ to the 3^rd^ of the VH provocations. The primary behavioral measure will be avoidance responses (latency in seconds between VH provocations 1–2, and 2–3). The primary physiological index of VH reactivity will be the mean difference in end-tidal CO_2_ during the resting baseline vs recovery phase.

#### Theoretically-relevant and general competing predictor variables

Participants will complete the following self-report measures of constructs related to CO_2_ reactivity and/or expected to be predictive of EBT non-response: ASI-3 [119], Distress Tolerance Index (DTI) [88], Brief Experiential Avoidance Questionnaire (BEAQ) [120], IUS [91], and Safety Behavior Assessment Form (SBAF) [121]. Additional control predictor variables include sex assigned at birth, gender identity, number of diagnoses (s measured by the SCID-5), and comorbidity symptom severity (as measured by the DSM-5-TR Self-Rated Level 1 Cross-Cutting Symptom Measure).

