CO_2_ reactivity can also be influenced by a number of psychological factors. We have selected control variables relevant to CO_2_ reactivity that are not related to orexin activity, including: (1) anxiety sensitivity (AS; the tendency to perceive that anxiety-related symptoms and sensations have catastrophic consequences [82]), which operates as a transdiagnostic risk factor for the maintenance of anxiety pathology [83] and a reliable predictor of reactivity to interoceptive challenges, including CO_2_ [84, 85] and VH [78, 86]; (2) distress intolerance (DI); notably, although AS can be conceptualized as a measure of distress intolerance (DI), there is variability in prediction and reactivity with alternative measures of DI [87–89]); (3) experiential avoidance (EA) [90]; (4) Intolerance of uncertainty (IU) [91, 92], a putative transdiagnostic risk factor for the maintenance of anxiety and related disorders and EBT non-response [93–99]; and finally, (5) a behavioral index of subtle avoidance behaviors that may interfere with extinction [100]. In sum, AS, DI, EA, IU, and related avoidance tendencies all share variance with CO_2_ and VH reactivity, but like VH, should be a poor marker of orexin activity. Finally, to demonstrate that the CO_2_ derived biomarker offers incremental predictive utility, we will also include standard, albeit unreliable, clinical and demographic predictors of EBT non-response [18–30].

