### Sample size and data analytic approach

Simulation work has shown that large sample sizes are required to develop accurate predictive models of treatment response [102, 103]. Our own statistical simulation shows that given the two-site, split-half validation design, we require 300 participants per site—at least 300 to develop the model and another 300 to adequately validate it in this Stage 1 model. The reality is that underpowered studies likely detect only the largest effects, and multivariate models based on them yield unstable predictions that overfit the sample data and perform poorly out-of-sample [104, 105]. As pointed out by Kessler and colleagues, “The inevitable conclusion is that samples much larger than those in existing mental disorder randomized clinical trials are required to develop useful personalized treatment recommendations” [106]. The overarching message of the statistical learning literature and our own simulations used to develop this proposal is “go big or go home”.

Our primary objective is to build a model predicting EBT non-response using a multivariate combination of candidate predictors. One set of predictors constitutes what we consider our “control” model; these include “traditional” prognostic factors and psychological variables (see Table 1). The addition of a second set of predictors, corresponding to our proposed measures of reactivity to CO_2_ and VH, constitutes our “experimental” model. We have two key hypotheses that we aim to test: (1) the experimental model will outperform the control model when predicting never-before-seen data, establishing the additive predictive value of assessing reactivity measures prior to initiating treatment; and (2) when predicting never-before-seen data, a model that excludes VH reactivity measures will outperform a model that excludes CO_2_ reactivity measures, establishing that the additive predictive value is specific to CO_2_ reactivity.

**Table 1 Tab1:** Schedule of assessments

Measurement Domain	Screen	Biomarker Visit	Treatment (Weeks 1–12)	Follow-up (Weeks 13, 24)

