***Control Predictor Variables***				
Sex assigned at birth, Gender identity, Diagnosis, Comorbidity symptom severity	X	X		

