### Participants

The transdiagnostic sample will consist of 600 participants. Inclusion criteria include: (1) a primary DSM-5 diagnosis of PD (with or without agoraphobia), SAD, GAD, OCD or PTSD; (2) a score of 8 or greater on the Overall Anxiety Severity and Impairment Scale (OASIS) [107]; (3) ages 18–70; (4) willingness and ability to provide informed consent and comply with the requirements of the study protocol; and (5) proficiency in English (because many assessment instruments have only been validated in English). Exclusion criteria include: (1) a lifetime history of bipolar or psychotic disorders; substance use disorders (other than nicotine) or eating disorder in the past 6 months; serious cognitive impairment; (2) active suicidal ideation with at least some intent to act with or without a specific plan (i.e., a rating of 4 for suicidal ideation on the Columbia-Suicide Severity Rating Scale; CSSRS) [108] or suicidal behaviors (actual attempt, interrupted attempt, aborted or self-interrupted attempt, or preparatory acts or behavior) within the past 6 months; (3) medical conditions contraindicating CO_2_ inhalation or VH (e.g., cardiac arrhythmia, cardiac failure, asthma, lung fibrosis, stage 2 high blood pressure, epilepsy, or stroke); (4) pregnancy or lactation; (5) ongoing psychotherapy directed toward the primary disorder; or (6) pharmacological treatment started within 8 weeks prior to the screen (participants “stable” on their medication regimen will be included and their medication status will be included as a variable in the model).

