##### Definition of non-response

Participants will be classified as non-responders if their CGI—Improvement (CGI-I) score is 3 or above OR if their OASIS score has not improved by at least 4 points.

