Hypothesis testing will be based on a series of model comparisons. All models will be fit to the train site and used to predict the probability of treatment response at the test site. These probabilities will be used to generate an ROC curve for each model’s ability to discriminate treatment responders from non-responders. Significant differences between curves will be evaluated using DeLong’s test for two correlated ROC curves as implemented by the R package “pROC”. The following model comparisons will be performed:All candidate predictors vs. excluding CO_2_/VH reactivity measures. This comparison addresses the question: do the novel measures of CO_2_/VH reactivity add predictive value beyond traditional—and easier to collect—measures like diagnosis or symptom severity? We hypothesize that the addition of the reactivity measures will significantly improve model performance. If CO_2_ reactivity is completely confounded with these competing predictors, then adding it to the model will not result in any predictive gains; CO_2_ reactivity can only improve model predictions if it provides unique information that is not captured by “confounders”.CO_2_ vs. VH reactivity. Finally, if the above model demonstrates the value of collecting CO_2_ reactivity measures, we will next assess does CO_2_ reactivity specifically predict treatment non-response (by revealing something about the underlying biology), or is it merely heightened sensitivity to the physiological sensations that are common to both CO_2_ inhalation and hyperventilation? Qualitatively, if VH reactivity has no predictive utility, then the statistical learning algorithm will have penalized these measures out of the model entirely by this point. However, the hypothesis of mechanistic specificity will be more formally tested by comparing a model that includes just CO_2_ reactivity measures to one that includes just VH reactivity measures. Note that the ability to perform a head-to-head comparison like this is one of the advantages of comparing ROC curves in an independent test set; the models do not need to be nested as they would when performing likelihood ratio tests on model fits.

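### The control-model predictors are stated inconsistently across sections, and baseline OASIS is never named among them although OASIS change helps define non-response

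*Protocol article*

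**What the plan says.** The control set is described in several places in the protocol article.

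- *Sample size and data analytic approach* defines the control model as traditional "prognostic factors and psychological variables (see Table 1").
- Table 1, control predictor row: "Sex assigned at birth, Gender identity, Diagnosis, Comorbidity symptom severity". A separate row holds the five questionnaires (ASI-3, DTI, BEAQ, IUS, SBAF). OASIS appears only among the outcomes, with a screening measurement, and demographics appear under screening.
- *Theoretically-relevant and general competing predictor variables*, after naming the questionnaires: "Additional control predictor variables include sex assigned at birth, gender identity, number of diagnoses (s measured by the SCID-5), and comorbidity symptom severity". The severity item is scored on the DSM-5-TR Level 1 cross-cutting measure.
- *Participants*, on people stable on medication: "their medication status will be included as a variable in the model".
- *Model development and validation strategy* describes the comparator as traditional, easier-to-collect "measures like diagnosis or symptom severity". It argues that CO2 reactivity can improve prediction only by carrying information that the competing predictors lack.
- *Optimizing the methodological approach* promises "standard, albeit unreliable, clinical and demographic predictors of EBT non-response" without listing them.

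OASIS also governs entry and outcome. Entry requires "a score of 8 or greater on the Overall Anxiety Severity and Impairment Scale (OASIS"). A participant is a non-responder if CGI-I is 3 or above, "OR if their OASIS score has not improved by at least 4 points".

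**The concern.** An incremental-value claim is only as good as the model it is measured against. The article's argument that any gain must be unique to CO2 holds only for competing variables that are actually in the comparator. Two analysts working from this text could build different control models, and so report different AUC gains and different p-values for the first hypothesis.

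Baseline OASIS matters most. A fixed-point threshold ties the outcome to the starting score, so baseline OASIS may predict non-response for reasons that have nothing to do with extinction learning. The primary subjective CO2 index is self-reported anxiety, and OASIS is also self-reported, so shared variance is plausible. If baseline OASIS is left out, CO2 reactivity could stand in for it.

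**Working it through.** **1. The statements side by side**

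| Variable | Table 1 control row | Assessment text | Elsewhere |
|---|---|---|---|
| Primary diagnosis | Diagnosis | not named | comparator example in the analysis section |
| Number of diagnoses | not named | named | – |
| Medication status | not named | not named | in the model (*Participants*) |
| Symptom severity | comorbidity only | comorbidity only | symptom severity, comparator example |
| Baseline OASIS | not named | not named | entry criterion and outcome only |
| Age | not named | not named | entry criterion only |

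Diagnosis and medication status are each in the plan somewhere, so for them the fault is inconsistency. Baseline OASIS and age are named as predictors nowhere.

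**2. Does count versus category of diagnosis matter?** The power section gives response rates of 0.53, 0.45, 0.47, 0.43 and 0.59 in five equal groups, mean 0.494. For a five-level predictor, AUC = 0.5 + Σ|rᵢ − rⱼ| / (2 × 5² × r̄(1 − r̄)), summed over the ten pairs.

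- Sum of pairwise differences = 0.80.
- r̄(1 − r̄) = 0.494 × 0.506 = 0.24996.
- AUC = 0.5 + 0.80 / (50 × 0.24996) = 0.564.

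The whole control model is assumed to reach 0.63. Which disorder a patient has therefore carries some signal, and a count of diagnoses does not record it.

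**3. How the fixed threshold depends on baseline.** 4/8 = 50% and 4/16 = 25%. Assume, for illustration, proportional improvement that is independent of baseline and normal with mean 42% and SD 30%. Neither figure is in the documents.

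- Baseline 8: P(improvement < 50%) = Φ((0.50 − 0.42)/0.30) = 60.5%.
- Baseline 16: P(improvement < 25%) = Φ((0.25 − 0.42)/0.30) = 28.5%.
- With rounding to whole points: 52% and 25%.
- Over means of 30–50% and SDs of 20–40%, the difference between baseline 8 and 16 is 20 to 46 percentage points.

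These figures are for the OASIS limb only. The CGI-I limb dilutes them. Under similar assumptions the composite is 58% against 45%, and baseline OASIS alone has AUC 0.60 for the OASIS limb but only about 0.54 for the composite.

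**4. Power, starting from the plan's own figure.** Stated: 92.2% for AUC 0.73 against 0.63, 300 test participants, directional DeLong test at 0.05. The covariance structure is not given, so exact reproduction is not possible.

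- Hanley–McNeil variances with an assumed correlation between the two AUC estimates: 90.9% at 0.4 and 94.7% at 0.5. The stated figure lies between.
- Simulated DeLong tests on nested binormal scores: 94.9%.
- A version trained on 300 and tested on 300 (ridge logistic, 10 control and 8 reactivity predictors, assumed): 95.0%.

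The stated figure is plausible. The rows below should be read against 94.9% and 95.0%.

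*Additions overlap fully with CO2/VH (experimental AUC stays at 0.73):*

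| Control AUC | Power, known weights | Power, trained weights |
|---|---|---|
| 0.65 | 90% | – |
| 0.66 | 87% | 78% |
| 0.67 | 81% | – |
| 0.68 | 75% | 57% |
| 0.70 | 56% | 30% |

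*Additions independent of CO2/VH (both AUCs rise; known weights):*

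| Control / experimental AUC | Gain | Power |
|---|---|---|
| 0.65 / 0.74 | 0.09 | 94% |
| 0.67 / 0.75 | 0.08 | 93% |
| 0.70 / 0.77 | 0.07 | 91% |

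The documents do not say how far baseline OASIS and the other additions would raise the control AUC, so the rows are scenarios.

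**The case against.** A reader might infer that four variables (baseline OASIS, primary diagnosis, medication status and age) are omitted, and that CO2 is being tested against a needlessly weak comparator. The documents do not support that. The control model is defined through Table 1, which lists diagnosis, and the analysis section repeats it. Medication status is expressly placed in the model. The text list is introduced as inclusive, not exhaustive, and clinical and demographic predictors are promised in general terms. Symptom severity in the analysis section may be meant to cover baseline OASIS. This is also a condensed article, and an itemised covariate list may well stand in a fuller document.

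The consequence is not shown either. The documents give no correlation between CO2 reactivity and severity, and they describe CO2 responses as arising from systems distinguishable from general trait anxiety. For the actual composite outcome, the illustrative AUC of baseline OASIS is close to chance.

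Most of this stands, and it limits the point to what is written here. It does not remove the point. The statements that are printed disagree with one another. The only severity measure that either list names is comorbidity severity, which the text ties to the cross-cutting instrument. An inclusive verb and a general promise do not tell an analyst whether the baseline of the outcome scale belongs in the control model. Age being unnamed would not be a finding on its own. It belongs in the list only because the list has to be settled anyway.

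**Conclusion.** The point holds as one of inconsistent specification, with one substantive gap: no statement puts the baseline value of the outcome scale into the control model. That follows from the text alone and needs no assumption.

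A reader might go further and conclude that the CO2 gain is inflated. The documents do not support that step. Inflation requires the unlisted variables to share information with CO2/VH reactivity, and nothing given fixes how much they share, or in which direction any bias would run. The baseline-dependence figures rest on an assumed improvement distribution, and the power figures on assumed control AUCs and two extreme overlap scenarios. Between those extremes the consequence runs from almost no change in power with a modestly smaller AUC gain to a clear loss of power. With full overlap, the lower power would reflect that reactivity has less unique information to offer, which is the quantity the first hypothesis is about.

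The correction is worth making before models are fitted. It is not a reason to doubt the design.

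**What to change.** Reconcile *Sample size and data analytic approach*, the Table 1 control row, *Participants*, *Theoretically-relevant and general competing predictor variables* and *Model development and validation strategy* into one pre-specified control set. Use it unchanged in the control, experimental, CO2-only and VH-only models. Name in it:

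- baseline OASIS, being the same score from which the 4-point change is computed;
- primary diagnosis in five categories, and number of diagnoses;
- medication status, age, sex assigned at birth and gender identity;
- comorbidity symptom severity;
- the five questionnaires.

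All of these are already collected or obtained at screening or the biomarker visit, so the cost is wording. With medication status as a single indicator, the model gains about four terms relative to Table 1 if diagnosis is already in five categories (OASIS, number of diagnoses, medication, age). Relative to the text list it gains about seven (OASIS, four diagnosis indicators, medication, age). All are penalized. The price may be a smaller observed AUC gain and, if the additions overlap with reactivity, lower power than stated. The power simulation could be rerun with the settled list to show the range.

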#### Symptom severity

Prior to each treatment visit (Weeks 1–12), at posttreatment (Week 13) and at follow-up (week 24), an independent evaluator (IE; telehealth) will administer the Clinical Global Impressions (CGI) scales [122]. Participants will also complete the OASIS and the Patient Health Questionnaire (PHQ-9) as well as the symptom severity measure corresponding to their primary diagnosis (Panic Disorder Severity Scale-Self Report Version [PDSS-SR; PD] [123], SPIN [SAD] [114], GAD-7 [GAD] [124], DOCS [OCD] [116], or PCL-5 [PTSD] [117]) prior to the meeting with the IE. Every 3 weeks participants will also be asked to complete several treatment process measures that are not related to the primary study aim. IE training will involve completion of a 3-h workshop and reliable rating (> = 80%) of interviews with test subjects. IE’s will also complete quarterly ratings of test cases to prevent rater drift.

